#### 2.4.2. Exclusion Criteria

A potential subject (parent–infant dyad) who meets any of the following criteria will be excluded from participation in this study:−Infant’s hospital stay shorter than 7 days;−Infant with severe congenital or syndromal anomaly;−Infant with critical illness who is unlikely to survive;−Parents with current severe psychosocial problems;−Involvement of child protective services in the family;−Parents not able or not willing to fill out questionnaires in English or Dutch.

Healthcare professionals of whom the employment in a participating centre is discontinued through the course of the study, will be excluded from further measurements.

### 2.5. Procedures

All ten participating hospitals start the control phase, delivering SNC as they did prior to the study. Subsequently, randomisation will determine in which order the neonatal wards will start with the implementation of FCR according to the FICare principles. The outcomes will be measured at the individual level (parental and neonatal outcomes) and at the cluster level (healthcare professional-outcome measures, adherence to the intervention and cost-effectiveness). Given that the intervention includes active participation of parents in neonatal care and medical rounds, blinding is not possible for participants and researchers. However, as the outcomes cannot be influenced by the researcher and are unlikely to be influenced by the parents’ knowledge of the intervention, the risk of performance and detection bias is assumed very low.

In the three months preceding the intervention period (the implementation period), FCR and FICare principles will be implemented on the neonatal wards of the participating hospitals. We will develop and use a universal implementation strategy of FICare, adjusted to the Dutch setting, in close collaboration with the Dutch neonatal parent and patient advocacy organisation (Care4Neo). To ensure feasibility and sustainability of the intervention in all participating sites, an FICare-working group will be formed at each site. Each participating centre is responsible for the recruitment of participants of their own FICare-working group. To achieve the broadest possible representation, FICare-working groups will include neonatal nurses, paediatricians, veteran parents and other neonatal healthcare professionals (such as psychologists or physiotherapists). Veteran parent(s) will be recruited through the patient organisation (Care4Neo) or via the outpatient clinic by paediatricians. Training and guidance of the veteran parents will be coordinated by Care4Neo. The FICare-working group will be responsible for tailoring the intervention to the specific neonatal ward, in cooperation with the research team, and the planning and execution of the staff and parent training.

The four pillars of FICare will be translated into a package of education and other materials adapted to the Dutch setting, to support FICare in all participating sites, including the following components [15]:Education of parents:−Information on the hospital admission and care of an infant, including a digital application (NeoZorg application);−The possibility to keep track of (medical) information in a diary and/or digital application (NeoZorg application, see further);−Educational and thematic meetings (physical and/or digital) with other parents, led by either healthcare professionals (nurses, paediatricians and/or paramedic staff) or veteran parents.Education of healthcare professionals:−Comprehensive e-learning on FICare and FCR, developed by the research group. The e-learning comprises the following modules:−Theoretical background and historical context of FICare and FCR;−Implementing FCR in practical settings;−Coaching of parents by healthcare professionals;−Explanation of the existing (co-)interventions SFR and family-centred care;−Understanding the principles of FCR and shared decision-making.−Training in FICare principles: the research group has designed training materials for effective collaboration and communication with parents, parent participation and shared decision-making. These training materials draw from both existing literature and the valuable insights available on the Canadian website dedicated to FICare (www.familyintegratedcare.com, accessed on 22 May 2022).

The training sessions consist of three modules, recorded as lectures, and are further discussed with the local staff by the respective FICare workgroups. The three modules covered are:−The theory and practical application of FICare and FCR;−The role of healthcare professionals within the context of FICare;−Emphasizing shared decision-making.

The intended audience for this training includes nurses, residents, and paediatricians, while also recommending paramedical staff to participate, at the very least, in the e-learning modules.Psychosocial support:−Facilitating contact and peer support for parents with veteran parents, both during admission and after discharge;−Support by paramedical staff (e.g., psychologist, preverbal speech therapist, physiotherapist, social worker).Environment of the neonatal ward:−FICare whiteboard/communication board, at which parents can track for example their participation progress and information on their infant;−Facilities for skin-to-skin contact and expressing human milk on the ward;−24/7 access to the ward;−Facilities to be (digitally) present during medical rounds (i.e., including video conference or telephone calls).

The NeoZorg application (Synappz Digital Healthcare^®^, Oss, The Netherlands)—originally developed for level 3 neonatal care and in use in the NICU in Amsterdam—was adapted and innovated especially for this study by our research group with extra information suitable for level 2 neonatal care. NeoZorg is a digital platform for parents with an infant in a neonatal ward, and can be used as an information and education medium for parents. The application provides a library with extensive expert information on relevant topics regarding neonatal care for parents. A special section is devoted to FICare and FCR videos. In addition to this library function, the application offers a diary function for parents to keep track of their child’s clinical condition and development during hospital stay. Parents can save notes and photographs and are provided space to write about their experiences and mental state. They can also enter clinical information such as growth, intake and human milk production, which can then be displayed in graphs. Through these functions, parents can keep up with the development of their infant’s clinical condition (in the Netherlands, real-time medical chart involvement is not usually provided). Alongside these functions, the application can send messages to parents with relevant information based on the stage of development and admission of their infant. Healthcare professionals can send parents pictures or short messages through a communal tablet that is present at the ward. As the application is purely intended to support parents, no study data will be gathered through the application. Given the high rates of smartphone ownership in the Netherlands, it is anticipated that every parent will have access to and be able to use the app. However, it is important to note that the app will not replace the paper diary in hospitals where it is already in use. Therefore, if parents choose not to utilise the app or face any other limitations, they can still opt for the traditional paper diary.

### 2.6. Control Treatment: Standard Neonatal Care without FCR

In the control period, standard neonatal care (SNC) will be provided. Although attention is given to parents in most current neonatal care, sometimes even based on the family-centred care principles, structural involvement of parents in care according to the FICare pillars is not yet implemented. Medical rounds are held between healthcare professionals without the (structural) presence of parents. Parents are updated by the nurses daily, or whenever a parent is present. Usually, parents are also updated at least weekly by their attending physician. Most care (both daily and medical care) for the infants is provided predominantly by the nurses. Parents usually have (unlimited) access to the ward but are not supported by the concept of FICare.

### 2.7. Interventional Treatment: Family-Centred Rounds Embedded in the FICare Principles

Families that are included during the intervention period will participate in family-centred rounds, while being supported by the principles of FICare as described in Section 2.5. In FCR, parents actively participate in the medical rounds with healthcare professionals and decisions are made based on shared decision-making, whenever appropriate. Not only are parents informed about the clinical condition of their child, they can ask questions and share their own valuable information on their child [20,21]. Giving the parents the opportunity to take on their irreplaceable role during medical rounds, and actively participate in the process of shared decision-making, requires more than merely an invitation: both parents and healthcare professionals need to receive the appropriate support and education. In the intervention period, this support is provided based on the four pillars of FICare. Also, parents will have access to the NeoZorg application (Synappz Digital Healthcare^®^).

### 2.8. Primary Outcome

The primary outcome of the study will be the level of parental stress at discharge. The Parental Stress Scale: Neonatal Intensive Care Unit (PSS:NICU) is the most widely used instrument to measure parental stress and stressors arising from hospitalisation of an infant on the NICU [31]. It measures the parental perception of stressors that are arising from the hospitalisation of their child, with a variety of health problems on any type of inpatient unit [32]. The design of this tool emphasises the 3 dimensions of the surroundings and experiences on an NICU: the environment of the unit (sights and sounds; 5 items), the appearance of the infant (14 items) and alterations in the parental role (7 items). The 3 subscales show an internal consistency (Cronbach’s α) of 0.73–0.94 [31,32]. A total of 26 items are scored from “not stressful at all” to “extremely stressful”, and both a subscore for each domain and a total score (ranging from 0 to 130) are given. Parents will be asked to fill out the PSS:NICU at discharge. The primary outcome will be defined as the mean difference in total PSS-NICU scores at discharge between the intervention and the control group.

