#### 2.4.1. Inclusion Criteria

Recruited patients will be patients admitted to a level 2 neonatal ward for 7 days or more. To be eligible to participate in this study, a subject (parent–infant dyad/triad) must meet all of the following criteria:−Infant requiring hospital admission directly (within 24 h) after birth;−Parent are 18 years or older;−Written, informed consent of both parents/legal guardians (compliant to the regulations of the Central Committee on Research Involving Human Subjects).

All healthcare professionals (nurses, nurse practitioners, residents, paediatricians and neonatologists) that are employed on the neonatal ward during the study are eligible to participate regarding healthcare professional outcomes.

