Parent–infant bonding will be measured using the Maternal Postnatal Attachment Scale (MPAS) [41]. The MPAS is a self-report tool containing 19 items with responses on a two- to five-point scale, reflecting the key experience of the mother-to-infant bond. The total score is formed by the sum of the 19 item responses. As each item score ranges from 1 (low attachment) to 5 (high attachment), to provide equal weighting of all items, the total score ranges from 19 to 95. The original version is based on a three-dimensional structure: pleasure in interaction with the infant, lack of negative feelings towards the infant, and sense of confidence and satisfaction in their competence as a parent [41,42,43]. Both the English and Dutch (translated) version show strong internal consistency [41,42]. For fathers, the Paternal Postnatal Attachment Scale (PPAS) will be used [44].

Parental mental wellbeing will be assessed longitudinally until the (corrected) age of 12 months of the infant. For this, three questionnaires will be used, sent to parents at admission (for parents of infants born <35 weeks), discharge and at the (corrected) ages of 3, 6 and 12 months of the infant. The subjects of mental wellbeing measured are stated below.

Post-traumatic stress symptoms will be assessed using the PCL-5. The PCL-5 is a diagnostic tool for post-traumatic stress disorders, adjusted to the DSM-5 [45,46]. The PCL-5 contains 20 items in a 4-factor model based on symptom clusters: intrusion, avoidance, negative alterations of cognitions and mood, and alterations in arousal and activity. The original (English) version shows a good internal consistency with a Cronbach’s a of 0.94, and has been validated in parents with satisfactory psychometric properties [47]. The PCL-5 has been translated to Dutch [48], and the translated tool shows an internal consistency similar to the original English version [49].

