### 2.10. Statistical Procedures

#### 2.10.1. Sample Size Calculation

Based on previous research, a mean difference of 13 points (0.5 standard deviations) on the total score of the PSS:NICU is expected between the intervention and control groups after implementation of FCR and FICare [25,26]. The stepped-wedge design will have a total of 7 steps of 3 months each. At each step, two hospitals will implement the FICare intervention. One step will be an implementation (or wash-out) period. With an expected amount of 25% missing data, a power of 80%, intra-cluster correlation of 0.01 and an eta of 0.5 times the estimated effect, we aim to include 600 infants and their parents divided over 10 clusters.

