#### 2.10.2. Statistical Analysis

All analyses will be performed based on an intention-to-treat principle to minimise attrition bias. A sensitivity analysis with a per protocol analysis, including, for instance, only the infants and families who have not been transferred from the study site to another hospital before discharge home, will also be performed. Possible bias due to differential withdrawal or study drop-out will be assessed in this per protocol sensitivity analysis as well. We will consider performing a subgroup analysis based on clinical characteristics, to adjust for differences in (severity of) infants’ medical conditions.

Baseline characteristics of the intervention and control group will be compared using student *t*-tests for continuous normally distributed variables, and Chi-square tests for categorical variables. Non-parametric tests will be used for variables that do not follow a normal distribution. Missing data will be handled by multiple imputation chain equations (mice) [70] with adjustment for clustering [71]. Rubin’s rules will be applied to pool the results of the different imputed dataset [72]. As described and proposed by the Panel on Handling Missing Data in Clinical Trials, we will carry out sensitivity analyses with different missing data strategies adjusted for clustering [73]. We will consider missing completely at random, missing at random, and missing not at random approaches.

With a generalised linear mixed modelling (GLMM) analysis, we will analyse whether parental stress at discharge is decreased after the intervention. We will include the factor “cluster” (hospital) as random effects, and “step” will be included as fixed (time) effect. In a secondary analysis, adjustment can be applied for possible confounders, such as (medical) characteristics of the infant during hospital stay. Adjustment for possible time effects will be made.

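### Both parents may score the primary PSS:NICU, but the primary model has no family level and no rule gives one score per family; if both scores enter, the standard error is too small

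*Protocol article*

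**What the plan says.** - **Who answers.** Section 2.8: "Parents will be asked to fill out the PSS:NICU at discharge". Table 1 gives parents as the subject for the PSS:NICU at discharge, and uses mothers as a separate label where only mothers are meant (human milk).
- **Who is enrolled.** Section 2.4.1: "a subject (parent–infant dyad/triad) must meet all of the following criteria". A triad has two parents. The same section requires "Written, informed consent of both parents/legal guardians".
- **Fathers respond to questionnaires.** Section 2.9.2: "For fathers, the Paternal Postnatal Attachment Scale (PPAS) will be used".
- **Primary comparison.** Section 2.8: "The primary outcome will be defined as the mean difference in total PSS-NICU scores at discharge between the intervention and the control group". Nothing says whose score is used when there are two, or how two are combined.
- **Primary model.** Section 2.10.2: "We will include the factor “cluster” (hospital) as random effects, and “step” will be included as fixed (time) effect". No family effect, family summary or family-level robust variance appears in the article.
- **Sample size.** Section 2.10.1: "we aim to include 600 infants and their parents divided over 10 clusters". The only correlation entered is the hospital intra-cluster correlation of 0.01.

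**The concern.** Two parents of one infant are in the same hospital and the same period, and so have the same exposure. They also rate the same things: 14 of the 26 items concern the infant's appearance and 5 the sights and sounds of the ward. Their scores should be positively correlated. A model with only a hospital intercept treats the two scores as independent given hospital and step. The hospital intercept cannot absorb the correlation, because it is shared by every family in the hospital and is planned to carry only 1% of the variance.

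Because exposure does not vary within a family, ignoring a positive correlation always works in one direction: the standard error is too small, the confidence interval too narrow and the type I error above nominal. This is the primary analysis. The same issue would reach the PCL-5, PROMIS and SDM-Q-9 if the same model were used for them.

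**Working it through.** **Inputs from section 2.10.1.** Difference 13 points = 0.5 SD, so SD = 26 and total variance = 676. Hospital ICC 0.01. Eta = 0.5 × 13 = 6.5. Seven periods, two hospitals per step, ten hospitals, one implementation period per hospital. 25% missing, 80% power, 600 infants.

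**Assumptions.** Two-sided 5% test; implementation period not analysed; normal approximation. The article does not say whether eta is a variance or an SD, so both are shown. The within-couple correlation ρ (within hospital and period) is not in the documents and is varied.

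**Set-up.** Analysed cells: 10 × (7 − 1) = 60. Families analysed: 600 × 0.75 = 450, or 7.5 per cell. Hospital variance: 0.01 × 676 = 6.76. Residual variance: 676 − 6.76 = 669.24. The model has fixed periods, a random hospital intercept and a random treatment effect across hospitals. The SE is the square root of the treatment element of (X′V⁻¹X)⁻¹.

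**Step 1: the plan's own figure.** With one score per infant, the residual variance of a cell mean is 669.24 / 7.5 = 89.23. With eta as a variance of 6.5, SE = 4.62 and power = Φ(13/4.62 − 1.96) = 80.3%. Exactly 80% needs 446 analysed, and 446 / 0.75 = 595 recruited, against 600 stated. With eta as an SD of 6.5, 588 analysed (784 recruited) would be needed. So 600 is recovered with one independent score per infant, on the variance reading of eta.

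**Step 2: both parents' scores entered.** There are 900 scores, 15 per cell. The naive model uses 669.24 / 15 = 44.62 for the residual variance of a cell mean. The correct value is 44.62 × (1 + ρ): 49.08, 58.00, 66.92 and 75.85 for ρ = 0.1, 0.3, 0.5 and 0.7. At ρ = 1 it returns to 89.23, the one-score value.

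True type I error = 2 × [1 − Φ(1.96 × naive SE / correct SE)]. Power = Φ(13 / correct SE − 1.96). With eta as a variance:

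| ρ | Naive SE | Correct SE | Ratio | Type I error | Power, correct SE |
|---|---|---|---|---|---|
| 0.1 | 3.44 | 3.58 | 1.04 | 6.0% | 95% |
| 0.3 | 3.44 | 3.84 | 1.12 | 7.9% | 92% |
| 0.5 | 3.44 | 4.08 | 1.19 | 9.9% | 89% |
| 0.7 | 3.44 | 4.31 | 1.25 | 11.7% | 86% |

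For ρ = 0.5: 1.96 × 3.441 / 4.082 = 1.652, which gives 9.9%.

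**Step 3: sensitivity.**
- Eta as an SD of 6.5: naive SE 4.00; type I error 5.8%, 7.3%, 8.9% and 10.4%; power with the correct SE 88%, 84%, 81% and 77%.
- Eta = 0: type I error 6.0%, 8.1%, 10.2% and 12.2%.
- Partial response: if each parent responds independently with probability 0.75, the factor (1 + ρ) falls to (1 + 0.75ρ), since (4 × 0.5625 + 0.375)/1.5 − 1 = 0.75. The inflation shrinks but does not vanish.

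**Step 4: simulation of the written model** (3,000 runs per value, 450 families, both parents, eta = 0, z test). Type I error was 6.4% at ρ = 0, 9.6% at 0.3, 11.8% at 0.5 and 13.6% at 0.7. At ρ = 0.5 the mean naive SE was 3.32 against an empirical SD of 4.13. Analysing the family mean gave 6.2–6.5%. The excess over 5% that remains at ρ = 0, and with family means, comes from having only ten hospitals; the rest comes from the missing family level.

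**The case against.** The strongest reply is that the article never says each parent's score is a separate row. The target is counted in infants, and 600 can be recovered with one score per infant. Consent of both parents may serve only to enrol the infant, and the fathers' bonding scale says nothing about the PSS:NICU. The model sentence is condensed (it does not even list the intervention term), and family structure could sit in an analysis plan that is not shown.

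Much of this stands. A reader might infer that the trial will certainly analyse correlated scores as independent; the documents do not show that, so the point is conditional. It does not disappear, though. Table 1's distinction between parents and mothers makes two respondents per triad the natural reading, and the article does not leave the random-effects structure open: it states one that does not fit two scores per family. If one score per family is intended, nothing says which.

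Other extensions are also unsupported:
- **Bonding scales.** Mothers and fathers complete different instruments, and nothing suggests pooling them.
- **Twins.** The article does not mention multiples.
- **Sample size.** A second parent's score adds information, so the planned number is not undermined by this point.

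**Conclusion.** The point holds in conditional form. The article describes data with up to two primary scores per infant, a primary model without a family level, and no rule that yields one score. Run as written on both parents' scores, the model understates the primary standard error.

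The size depends on a correlation that the documents do not give. With both parents responding and eta as a variance, the correct SE is about 4%, 12% and 19% larger for correlations of 0.1, 0.3 and 0.5, and the type I error is about 6.0%, 7.9% and 9.9%. A reader might take a doubling of the false-positive rate as the expected result. That is the upper part of an assumed range; at 0.1 the effect is minor. The direction is certain for any positive correlation.

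**What to change.** State the unit of the primary analysis before the data are analysed, by one of two routes:

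1. **Keep both parents' scores.** Add a family random intercept nested in hospital and include parent role (mother/father) as a fixed effect.
2. **Use one score per family.** Prespecify it as a named parent's score or the family mean, and say what happens when only one parent responds.

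Carry the same structure into the multiple imputation model, and apply it to other outcomes where both parents answer the same instrument (PCL-5, PROMIS, SDM-Q-9).

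No new data are needed. The cost is a slightly wider confidence interval. Under route 1, power with the correct SE stays at 86–95% for correlations of 0.1 to 0.7 when eta is a variance. When eta is an SD it stays above 80% up to a correlation of 0.5 and is 77% at 0.7, still above the 71.8% from one score per infant on that reading. The sample size need not change for this reason.
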